### Data collection

An electronic clinical record form (eCRF) will be used to collect the data on each participant. Data will be entered into a web-based eCRF (Castor EDC) from electronic patient files by site personnel or by the study coordinators. The study participants will be identified on the eCRF through their unique trial identifier, allocated at the time of allocation. All source data recorded in the eCRF will be signed by the investigator or his/her appropriate designee. Course documents include original documents related to the trial, to medical treatment and to the history of the participant. The requirements for source data for this trial will be outlined in the study monitoring plan. All investigators and physicians will comply with the requirements of the national law with regard to collection, storage, processing, and disclosure of the patients’ personal information. The trial evaluation team, who will analyse that data, consists of the coordinating investigators in consultation with the principal investigators. They will receive only anonymised data. Patients’ personal data is stored locally at each study site in locked cabinets or electronically on encrypted secure drives. Physicians who are involved in the trial will be asked to report all AEs to the coordinating investigator. Serious AEs are reported using the online module (https://www.toetsingonline.nl).

### Analysis

#### Statistical analysis

Descriptive analysis will be performed for all baseline and demographic data. Normally distributed variables will be noted as mean with standard deviation (S.D.), and not-normally distributed variables will be noted as median with range or inter-quartile range (IQR) if stated. Categorical data will be noted as numbers and percentages of the total.

All randomised patients are evaluated for primary and secondary endpoints at 24 weeks. The primary analysis is based on intention-to-treat (ITT) principles. ITT analyses will be used for all clinical outcome variables. Every patient who has received at least one dose of study medication will be included in the ITT analysis. A per-protocol analysis will also be performed in patients who received >80% of the study medication. When deemed necessary, missing data will be dealt with accordingly with supportive statistical analyses (e.g. imputation or appropriate models) to assess the potential effects. These methods will be addressed in the final manuscript. Treatment effects will be analysed by comparing the difference in proportion with biochemical remission at 24 weeks between both groups. Values will be compared using Student’s *t* test, Mann-Whitney *U* test, Pearson test, Wilcoxon’s rank sum test, Wilcoxon signed-rank test, chi-square test or Fischer’s exact test, as appropriate. Time to remission will be tested and compared using a Kaplan-Meier survival analysis with log-rank test. Time to remission will be censored at 24 weeks. Significance of statistical differences is attributed to p <0.05. All statistical analyses will be performed with Statistical Package for Social Sciences (SPSS), version 22.0.

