### Study design and recruitment

CAMARO is a phase IV, randomised (1:1), open-label, parallel-group, multicentre superiority trial in 70 patients with treatment-naive AIH. All patients with established AIH according to the simplified criteria for the diagnosis of AIH [32] and who are considered for induction therapy will be eligible for the study. Eligibility will be assessed at the screening visit (SV) and patients will start with prednisolone according to the treatment schedules in Tables 2 and 3. A patient may enter the study at any time point in the first 4 weeks, as long as the prednisone schedule has been used for induction therapy. After informed consent, patients will be randomised in a 1:1 ratio to one of the two treatment arms. At 4 weeks, patients will consequently start with either azathioprine or MMF in dosages exactly according to the schedule (Tables 2 and 3). Eight follow-up visits are scheduled at weeks 4, 8, 12, 16, 20, and 24. The week 24 visit is the end of the treatment visit. After that, patients can continue azathioprine or MMF as assigned, as maintenance therapy. A trial flowchart is shown in Fig. 1.

**Table 2 Tab2:** Treatment schedule for patients 40–80 kg

Week	Prednisolone (mg/day)	Azathioprine (mg/day)	MMF (mg/day)
1	40	-	-
2	30	-	-
3	25	-	-
4	20	-	-
5	15	50	1000
6	12,5	50	1000
7[contact]
9+10	7,5	100	2000
From week 11 onwards	5	100	2000

*MMF* mycophenolate mofetil, *mg* milligrams

**Table 3 Tab3:** Treatment schedule for patients >80 kg

Week	Prednisolone (mg/day)	Azathioprine (mg/day)	MMF (mg/day)
1	60	-	-
2	45	-	-
3	30	-	-
4	20	-	-
5	15	50	1000
6	12,5	50	1000
7[contact]
9+10	7,5	100	2000
From week 11 onwards	5	100	2000

*MMF* mycophenolate mofetil, *mg* milligrams

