### Withdrawal from the study and replacement

Participants can leave the study at any time for any reason if they wish to do so without any consequences. The investigator can decide to withdraw a subject from the study for urgent medical reasons, such as (but not limited to) (a) occurrence of any AE or abnormality in a laboratory assessment which warrants the subject’s discontinuation from the trial, (b) patient noncompliance defined as refusal or inability to adhere to the trial schedule or procedures, (c) at the request of a regulatory authority, (d) the patient becomes pregnant, and (e) or the patients is lost to follow-up. If so, the patient will be followed and data will be recorded in an observational manner. All data generated up to the time of discontinuation from the study will be used for the intention to treat analysis and the reason(s) for discontinuation will be recorded.

Patients who participate in the study, but drop out for the study in the first 4 weeks will be replaced by new patients. If the participant is being withdrawn because of an AE, that AE must be indicated as the reason for withdrawal. Participants who withdraw from the study will be seen for a follow-up 4 weeks later. AEs and concomitant medication will be assessed and blood will be drawn.

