### Treatment groups and randomization

All participants, regardless of group allocation, will be treated with prednisolone induction therapy. The prednisolone dosage will commence at 40 mg or 60 mg per day, dependent on weight, and will be tapered according to a fixed schedule (Tables 1 and 2) which is based on the EASL Clinical Practice Guidelines [27]. We aim that all patients will eventually taper down to 5 mg prednisolone daily. Participants will have reduced prednisolone to 20 mg/day at week 4. Participants will be randomised 1:1, with a variable block randomization (block size 4, 6, 8) between azathioprine or MMF, stratified per participating centre for the presence of cirrhosis (yes/no). For randomisation of a patient, physicians can contact the study coordinators via telephone 24 h per day, 7 days per week in order to check the eligibility criteria and to verify whether informed consent has been obtained. Randomisation will be done by the study coordinator using the electronic case report form by Castor Electronic Data Management (Castor EDC). The study is an open-label trial which means that both patients and all research staff (including the primary caregiver and principal investigator) will be aware of the study arm allocated and thus are not blinded. Only outcome assessors will be blinded during the analyses. Therefore, unblinding will not occur in this study. Azathioprine and MMF will be packed and labelled as study medication according to Good Manufacturing Practice (GMP) guidelines by the pharmacy of the Leiden University Medical Center.

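### The plan contradicts itself on the primary analysis set, and its one-dose condition would let exclusion depend on known allocation under the ITT name

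*Protocol article*

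**What the plan says.** All references are to the protocol article.

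- **Statistical analysis**, on who is analysed: "All randomised patients are evaluated for primary and secondary endpoints at 24 weeks". The same paragraph then says: "Every patient who has received at least one dose of study medication will be included in the ITT analysis".
- **Treatment groups and randomization**, on what study medication is: "Azathioprine and MMF will be packed and labelled as study medication". Prednisolone is not named there. The same section states that patients and all research staff know the arm.
- **Study design and recruitment**, on timing: "A patient may enter the study at any time point in the first 4 weeks, as long as the prednisone schedule has been used". Randomisation follows consent, with no week fixed. Azathioprine or MMF begins at 4 weeks, and Tables 2 and 3 show neither drug in weeks 1 to 4.
- **Withdrawal from the study and replacement**: "Patients who participate in the study, but drop out for the study in the first 4 weeks will be replaced by new patients". The same section says: "All data generated up to the time of discontinuation from the study will be used for the intention to treat analysis".

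**The concern.** Under the first sentence on the analysed set, a patient randomised in week 2 who leaves in week 3 counts. Under the second, that patient has taken prednisolone only, has had no study medication, and does not meet the stated condition for ITT membership. The replacement rule then brings in a substitute.

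A one-dose condition is often defended on the ground that not starting treatment cannot depend on the arm. That defence needs blinding, and here patient and physician both know the allocation before the first dose. The decision to start can therefore differ by arm, and removing those who do not start breaks the randomised comparison for the primary endpoint. The result would still be reported as ITT. Because the text supports two denominators, the choice could also be made after the open-label data are known.

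**Working it through.** **1. The plan's own figure.** The Sample size calculation gives 32 per group for 75.0% v 38.8%, two-sided alpha 0.05 and power 0.80. Exact power of the two-sided Fisher test is 0.777 at 31 per group and 0.801 at 32, so 32 reproduces. Adding 10% fallout gives 32/0.9 = 35.6; the plan states 35. This point corrects neither figure. The 10% only gives a scale: 0.10 × 35 = 3.5, or three to four patients per arm.

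**2. The passages applied to one patient.** Take a patient who is randomised before week 4, learns the arm, and leaves before any azathioprine or MMF.

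| Rule | Status of this patient |
|---|---|
| All randomised are evaluated | In |
| At least one dose of study medication | Condition not met |
| Data up to discontinuation are used for ITT | Data used, but no week-24 ALT or IgG exists unless follow-up continues |
| Dropout in the first 4 weeks | Replaced; place in the analysis not stated |

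The rules do not give one answer.

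**3. Effect on a single result (assumed counts).** The documents give no number of undosed patients. Assume that 35 are randomised per arm, that 3 MMF patients leave undosed, and that all 3 count as non-remission when included.

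| Azathioprine | MMF, dosed only | Fisher p | MMF, all randomised | Fisher p |
|---|---|---|---|---|
| 16/35 (45.7%) | 24/32 (75.0%) | 0.024 | 24/35 (68.6%) | 0.090 |
| 14/35 (40.0%) | 24/32 (75.0%) | 0.006 | 24/35 (68.6%) | 0.030 |

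The first row crosses 0.05 and the second does not. The second is closer to the plan's own control rate of 38.8%. If the three are replaced and two of the replacements remit, the first row becomes 26/35 v 16/35, p=0.027, so replacement does not restore the all-randomised result.

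**4. Effect on type I error (assumed one-sided loss).** Suppose there is no true difference, 35 are randomised per arm, and k patients who would not remit are lost from one arm. The remission rate among the rest of that arm is p × 35/(35 − k). For k = 4 and p = 38.8% this is 38.8 × 35/31 = 43.8%, a bias of 5.0 points. For p = 70% it is 79.0%, a bias of 9.0 points. Type I error by full enumeration:

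| Common rate | Test | k = 0 | k = 2 | k = 4 |
|---|---|---|---|---|
| 38.8% | Chi-square, no replacement | 4.95% | 5.3% | 6.3% |
| 38.8% | Chi-square, replaced to 35 | 4.95% | 5.2% | 6.3% |
| 38.8% | Fisher, no replacement | 2.9% | 4.1% | 5.8% |
| 70% | Chi-square, no replacement | 5.05% | 7.0% | 13.1% |
| 70% | Chi-square, replaced to 35 | 5.05% | 6.5% | 11.5% |
| 70% | Fisher, no replacement | 2.8% | 5.1% | 9.7% |

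The inflation is slight for one or two losses near the plan's control rate. It becomes material with four losses at a high remission rate.

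**The case against.** The strongest reply is that the plan does not say undosed patients are dropped. The dosing sentence says who is included and does not contain the word only. The same paragraph has all randomised patients evaluated, and the withdrawal section keeps data up to discontinuation for ITT. The replacement sentence does not say that replaced patients leave the analysis. This stands as far as it goes: a reader might infer a firm rule that removes these patients, and the text does not establish one. It does contain a contradiction that permits removal. A dosing condition also has no purpose in an ITT definition if everyone randomised is in anyway.

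Three further limits stand.

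- **The window.** Four weeks between allocation and first dose is a ceiling. Entry may fall anywhere in that period, and patients have at least a week to consider the study, so the gap may be much shorter. The starting point of the first 4 weeks in the replacement rule is not stated. If it covers patients not yet randomised, replacing them is harmless. The schedule in Table 4 is not shown.
- **The motive.** MMF teratogenicity is the obvious arm-specific reason to leave, but it is discussed at the screening visit, and women of childbearing potential unwilling to use contraception are excluded. A change of mind after allocation remains possible, but it is not the open door that a reader might assume.
- **The size.** It is tempting to say that three exclusions reverse the trial's conclusion. That holds only for chosen counts; with 14/35 on azathioprine nothing reverses.

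**Conclusion.** The point holds as a contradiction in the definition of the primary analysis set. Applied literally, the dosing condition allows randomised patients to be left out and substituted after the arm is known, and the analysis would not then be ITT. The documents do not show that any patient was excluded in this way.

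The effect on the conclusion depends on how many leave undosed, from which arm, and how close the result is to 0.05. It ranges from no change to a crossing of the threshold with three patients. All the figures assume that every loss falls in one arm and is a non-remission; balanced losses would distort less. The matter should still be settled before lock, because it concerns the primary endpoint of a 70-patient trial and the repair is one of wording.

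**What to change.** Before database lock:

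1. Define the primary set as all randomised patients, analysed in the allocated arm, with no dosing condition.
2. Keep in that set any patient replaced after randomisation, whether or not a substitute was recruited. Count such a patient as not in remission if week-24 ALT and IgG are missing, and add a sensitivity analysis for missing data.
3. Use the one-dose condition only for the safety set and for a sensitivity analysis labelled modified ITT.
4. Reconcile the Statistical analysis section with the replacement section. State from when the first 4 weeks are counted and whether the rule covers randomised patients.

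Moving the time of randomisation is not needed. With 66 of 70 already randomised (Trial status), it would change procedure for about four patients and leave the definition unrepaired.

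The cost is wording, plus a possibly lower observed remission rate and power. As an outer case, let the whole 10% fallout count as non-remission in both arms: 0.9 × 75.0 = 67.5% v 0.9 × 38.8 = 34.9%. Fisher power at 35 per group is then 70% (chi-square 77%), against 80% by Fisher for the planned 32 per group. Patients who leave undosed should be only part of that fallout, so the loss from this change should be smaller.

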### Participants

The objective is to include 70 patients with treatment-naive AIH. The study will be conducted by the Dutch Autoimmune Hepatitis Working Group. Individuals who meet the entry criteria and complete the baseline visit will be enrolled in one of the participating centres. In total, fourteen centres are participating in the trial, including seven Dutch university medical centres. A list of study sites can be obtained at https://clinicaltrials.gov/ct2/show/NCT02900443.

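### Randomisation is stratified by centre and cirrhosis, but the stated primary comparison is pooled: still valid, but it leaves chance cirrhosis imbalance uncorrected and forgoes a little power (minor, almost free to fix)

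*Protocol article*

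**What the plan says.** Under Treatment groups and randomization, the protocol article allocates 1:1 by "with a variable block randomization (block size 4, 6, 8"), "stratified per participating centre for the presence of cirrhosis (yes/no"). Under Participants it gives the scale: "In total, fourteen centres are participating in the trial" and "The objective is to include 70 patients with treatment-naive AIH".

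Under Statistical analysis, the treatment effect is set out as "Treatment effects will be analysed by comparing the difference in proportion with biochemical remission at 24 weeks between both groups". A general list of tests follows. The entries that suit a binary outcome are "chi-square test or Fischer’s exact test, as appropriate", and neither is stratified. Time to remission is compared by a log-rank test, with no strata named. No covariate adjustment is mentioned anywhere. The section Sample size calculation also works with two unadjusted proportions.

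**The concern.** Cirrhosis is the only patient-level factor built into the allocation, yet the stated analysis makes no use of it. With so few patients per stratum many blocks stay unfilled, so the allocation cannot guarantee balance on cirrhosis across the trial. If cirrhosis affects remission, a chance imbalance passes straight into the primary estimate, and the precision available from a variable already recorded is not used.

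The allocation itself can hardly be changed now: Trial status reports 66 of 70 patients randomised. The analysis still can be.

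**Working it through.** **Inputs from the protocol article.** 14 centres; cirrhosis yes/no; N = 70; blocks of 4, 6 and 8; control rate 38.8%; MMF rate 75.0% in the calculation (70% in the sentence before it); two-sided alpha 0.05; 32 per group, 35 after fallout.

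**Assumed inputs.** The article gives no expected cirrhosis prevalence. The treatment-naive cohorts in Table 1 give 14/59 = 24%, 26/109 = 24% and 6/32 = 19%, so 24% is used, with 30% as a variant. It also gives no effect of cirrhosis on remission, so odds ratios from 1 (no effect) to 0.2 are tried.

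**1. The plan's own figure.** For 75.0% v 38.8% with 32 per group, exact enumeration gives 80.1% power for Fisher's exact test, 80.0% for the Yates-corrected chi-square and 86.6% for the uncorrected chi-square. The stated 32 is therefore reproduced by an unstratified Fisher or Yates test.

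**2. Strata.** 14 x 2 = 28, and 70/28 = 2.5 patients per stratum, below the smallest block. In simulation about 20-25 strata are occupied, 6-7 hold a single patient, and 11-12 of the 70 patients sit in strata containing only one arm.

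**3. Cirrhosis imbalance** (permuted blocks of 4/6/8, equal or skewed centre sizes):

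| Gap between arms | Planned scheme | Simple randomisation |
|---|---|---|
| 4 or more cirrhotic patients (24% prevalence) | 26-33% | 38-39% |
| 10 points or more (24-30%) | 16-26% | 33-36% |
| 20 points or more (24-30%) | 0.4-2.3% | 6-8% |

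The count gap is more frequent than the 10-point gap, although 4/35 = 11.4 points. The reason is that unfilled blocks also make the arms unequal in size. The gap in proportions is the one that moves the estimate.

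**4. Shift in the estimate.** Shift = imbalance x (remission rate without cirrhosis - rate with cirrhosis), at a marginal rate of 38.8% and 24% prevalence.
- Odds ratio 0.5: rates 0.425 and 0.270 (0.76 x 0.425 + 0.24 x 0.270 = 0.388). Shift = 0.10 x 0.155, about 1.6 points.
- Odds ratio 0.25: rates 0.456 and 0.173. Shift = 0.10 x 0.283, about 2.8 points.

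**5. Power** (change in points, Mantel-Haenszel stratified by cirrhosis minus pooled chi-square, about 35 per arm, no centre effect; ranges span separate simulations):

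| Assumed odds ratio | 70% v 38.8% | 75.0% v 38.8% |
|---|---|---|
| 1 | about -0.5 to 0 | -0.6 to 0 |
| 0.5 | +0.5 to +1.4 | -0.2 to +0.8 |
| 0.3 | +1 to +3.6 | +1.4 to +1.8 |
| 0.25 | not run | +1.5 to +2.1 |
| 0.2 | +3 to +5 | +2.5 to +3.2 |

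The pooled base is about 74-76% at 70% v 38.8% and 87-89% at 75.0% v 38.8%. With 2,500 runs, one power figure has a standard error of sqrt(0.87 x 0.13/2500) = 0.7 points, so differences of a few tenths are noise.

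**6. Stratifying on all 28 cells.** At 75.0% v 38.8%, power falls to 77.3-82.3%, a loss of 4.8 to 10.2 points against the pooled test when there is no centre effect.

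**7. Type I error.** Pooled test 4.4-4.8%; cirrhosis-stratified test 4.4-5.1%.

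**The case against.** The strongest reply is that this is a condensed article, that the full protocol and any SAP are not shown, and that adjustment for stratification factors is usually settled there. The test list is generic and applies as appropriate, and a Mantel-Haenszel risk difference is itself a difference in proportions. It stands that an unseen SAP may already settle the matter. But the article does state an analysis: a two-group comparison in which every test named for a binary outcome is unstratified, and a sample size on the same footing. The point concerns what is written.

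A second reply is that the remedy drops centre, although centre also defines the strata. A reader might infer that the analysis must mirror all 28 cells. The figures do not support that: matching the cells would cost about 5-10 points of power, so using cirrhosis alone is a practical choice.

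Two objections on size stand in full. A reader might infer that cirrhosis imbalance is likely, or that the stratification achieves little. A gap of 4 or more patients is absent in about 70% of trials, and the planned scheme does better than simple randomisation on every measure above. A reader might also infer a material loss of power. The gain depends wholly on assumed odds ratios, is nil at 1, and reaches 3-5 points only if cirrhosis is strongly prognostic.

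**Conclusion.** The point holds as a minor one. The stated primary comparison and log-rank test ignore the cirrhosis factor used in the allocation. The cost is an uncorrected chance imbalance (a gap of 4 or more patients in roughly 26-33% of trials; a shift of 1.6-2.8 points per 10-point imbalance) and a small amount of power (about 0 to 1.5 points for odds ratios of 1 to 0.5, up to about 3-5 at 0.2).

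It should not be read as saying that the pooled test is invalid or the estimator biased. Chance imbalance under randomisation does not bias the estimator, and simulated type I error stays near 5%. Nor does it explain any shortfall in power from the 70% and 75.0% both appearing in the sample size section, which is a separate matter.

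All sizes rest on an assumed prevalence of 24% (30% in some runs), assumed odds ratios, no centre effect and no missing outcomes.

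**What to change.** Before database lock, state in the SAP or by amendment:

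- Primary test: Cochran-Mantel-Haenszel, stratified by cirrhosis as recorded at randomisation.
- Estimate: the Mantel-Haenszel risk difference with 95% CI. With d the difference in remission proportions in a stratum, and n1, n0 and n its arm and total sizes, the estimate is the sum of w x d over the sum of w, where w = n1 x n0/n. There are only two strata.
- Do not stratify on the 28 centre-by-cirrhosis cells.
- Sensitivity: the pooled comparison, with one named test.
- Time to remission: log-rank test stratified by cirrhosis.

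The cost is a few lines of text. Cirrhosis status is already collected for allocation, and no extra patients or visits are needed. The only statistical downside is a power loss of under about 1 point if cirrhosis turns out not to be prognostic. Naming a single primary test also removes the choice between chi-square and Fisher's exact test that the article leaves open.
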